### Data collection, management, confidentiality, and analysis

#### Data collection, management, and confidentiality

The principal investigator has overall responsibility for the trial. The trial manager is responsible for trial procedures, day-to-day data management, and outcome analyses. Only data necessary to conduct the study is obtained. Data is collected by trained trial raters who are supervised by the trial manager. Collected data is handled by the trial manager and kept confidential and stored securely. Physical data (e.g., interview rating sheets) is kept in a locked file cabinet. Digital data (e.g., data obtained via smartphone in ecological momentary assessment) is stored in password-secured and encrypted files which are only accessible by the trial manager. The video recordings of the assessments are stored in encrypted files and will be deleted after completion of data collection. Personal identifiable information will not be released and is stored separately from research data. Research data is pseudonymized. An encrypting list which allows to allocate participant’s names to their trial ID and thus to their data is kept confidential. This list will be destroyed after termination of data collection. Only aggregated and anonymized data will be used for publication. All actions on data management as well as quantitative and qualitative data analyses are carried out by the trial manager and quality checked by the principal investigator. No data monitoring committee is convened for this study due to its short duration and the low risk of harm that can be expected from the intervention.

#### Analysis plan

Feasibility and acceptability will be analyzed by calculating descriptive statistics based on the intention-to-treat (ITT) population. Potential reasons for trial withdrawal will be examined by comparing baseline characteristics (e.g., symptom severity, sociodemographic variables, etc.) between participants who completed the trial and participants who discontinued their participation after randomization.

Clinical outcomes at baseline assessment (*t*_0_) and 6-month assessment (*t*_1_) will be summarized using descriptive statistics (i.e., frequency and percentages on binary and categorical variables; means, standard deviations, or medians, with minimum and maximum values for continuous variables) for each arm of the trial separately. Wait-list control and treatment group characteristics at baseline will be compared using Pearson chi-square tests for the categorical variables and the *t*-test or Mann–Whitney test for the quantitative variables.

Confirmatory analysis will be conducted for primary and secondary outcomes based on the ITT population. An ANCOVA adjusted for baseline values will be calculated with group allocation as between-subject factor and time as within-subject factor. Any variables that show significant group differences at baseline or are found to correlate with the primary outcome (e.g., age, gender, diagnosis, medication doses, duration of illness, symptom severity, etc.) will be entered as covariates. Effect sizes between and within treatment conditions will be assessed by calculating Cohen’s *d*. Missing values will be handled by multiple imputation, if missing completely at random [93]. All analyses will be carried out using validated statistical software.

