**Methods:**

Thirty participants diagnosed with a schizophrenia spectrum disorder and at least moderate motivational negative symptoms will be randomly assigned to either 24 sessions of “Goals in Focus” over the course of 6 months (*n* = 15) or to a 6-month wait-list control group (*n* = 15). Single-blind assessments will be conducted at baseline (*t*_0_) and 6 months after baseline completion (*t*_1_). Feasibility outcomes include patient recruitment, retention, and attendance rates. Acceptability will be rated by trial therapists and by participants at end of treatment. Primary outcome for effect size estimation is the motivational negative symptom subscale sum score of the Brief Negative Symptom Scale at *t*_1_ corrected for baseline values. Secondary outcomes include psychosocial functioning, psychological well-being, depressive symptoms, expressive negative symptoms, negative symptom factor scores, and goal pursuit in everyday life.

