### Study design

The study is conducted as a single-blind, parallel-group, randomized wait-list controlled feasibility trial (see Fig. 1 for study plan and assessment schedule) implemented at the psychology outpatient clinic at Universität Hamburg. The trial received approval from the ethics committee of the chamber of psychotherapists Hamburg (03/2020-PTK-HH) and has been preregistered at ClinicalTrials.gov (Identifier: NCT05252039) and Deutsches Register Klinischer Studien (Identifier: DRKS00018083). Any modifications to the protocol will be logged using these identifiers and, if required, will be communicated with the participants and secured by amendments to ethical approval. Outcomes will be measured at baseline (*t*_0_) and 6 months after baseline assessment (*t*_1_). Table 1 provides an overview of the trial design and assessment instruments. Recruitment started in 2020 and is planned to terminate in autumn 2023.

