#### Sample size

An a priori power calculation is not appropriate for this feasibility trial as the study aim is not to test efficacy. Nonetheless, we aim to examine first effect size estimates of “Goals in Focus” on our primary and secondary outcomes. These estimates will inform the sample size calculation for a future fully powered RCT. Based on the recommendations for feasibility studies [75] and on existing feasibility trials in this field [76, 77], the target for this feasibility study was set at *N* = 30 participants (*n* = 15 intervention group; *n* = 15 wait-list control group).

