#### Primary clinical outcome

The primary outcome for effect size estimation is measured with the baseline-adjusted “motivation and pleasure factor” (i.e., sum score of the seven items of this factor) of the Brief Negative Symptoms Scale (BNSS) at *t*_1_ [72, 73]. The BNSS is a 13-item semi-structured interview measuring negative symptoms on two factors, namely “motivation and pleasure” and “reduced expressivity” [81]. The “motivation and pleasure factor” includes seven items that measure the subscales of “anhedonia,” “avolition,” and “asociality” [82]. Symptoms are rated on a 7-point scale ranging from 0 “no impairment” to 6 “severe deficit”.

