“Goals in Focus” was developed to directly target the relevant motivational negative symptom domains by translating recent empirical research on factors and mechanisms underlying motivational negative symptoms into specified interventions. The comprehensive treatment approach is tested in a randomized controlled trial design which allows to eliminate a possible selection bias and to control for spontaneous remission effects. However, there are some limitations to our study design: this is a pilot trial with the main focus on feasibility and the sample of 30 participants is not sufficient for a reliable efficacy analysis. As likelihood of type 1 error inflation is high, results of significance tests cannot be interpreted, but effect sizes derived from the present study will be used for a priori sample size calculation for a subsequent fully powered RCT. The advantage of a wait-list control condition is that it allows a first estimation of effects and enables wait-list participants to later receive the same intervention. Also, diffusion effects between the conditions (e.g., patients from the wait-list group receiving information about the intervention from other patients, therapists including intervention elements in standard treatment) are unlikely due to the outpatient setting and the fact that treatment as usual is not provided by trial therapists. A disadvantage is that the wait-list comparator may artificially inflate estimates of the intervention effect, due to participants being held in a waiting position and less likely to initiate behavioral change on their own (e.g., as suggested by Cunningham et al. [94]). Additionally, the eligibility criterium of “being able to engage in weekly therapy sessions of 50 min” limits the generalization of effects to those who are not able to attend weekly sessions for the full-time range of 50 min. Other issues that warrant mention relate to the selected outcomes: since “Goals in Focus” aims at improving goal setting and achievement, the EMA of goal pursuit is of particular interest. However, participants’ adherence to an autonomously conducted 1-week survey might be reduced, which is why we did not select it as the primary outcome. Also, a long-term follow-up was not included at this point due to the primary focus being on acceptability, feasibility, and first estimates of efficacy. It also needs to be kept in mind, that the intervention only targets motivational negative symptoms and not expressive negative symptoms, the other relevant component of negative symptoms [72, 95]. However, we expect expressive negative symptoms to be indirectly affected by the intervention as suggested by results reported by Choi et al. [18] in relation to a similar treatment approach. Accordingly, expressive negative symptoms are evaluated as a secondary outcome. Similarly, the intervention does not target contextual factors, such as social deprivation or health-related issues that are likely to exacerbate negative symptoms, but expect the achievement of personal goals due to the intervention to partially improve participants’ challenging contextual factors as well.

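### The planned ANCOVA uses baseline as covariate and also has time as a within-subject factor; with only two assessments this contradicts the stated primary outcome and leaves several competing effect estimates

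*Protocol article*

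**What the plan says.** All references are to the protocol article.

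- **Analysis plan**, for primary and secondary outcomes: "An ANCOVA adjusted for baseline values will be calculated with group allocation as between-subject factor and time as within-subject factor". No group-by-time term is named, and no model term is identified as the treatment effect.
- **Study design**: "Outcomes will be measured at baseline" (t0) and 6 months later (t1). There is no third assessment, and the Discussion confirms that no long-term follow-up is included.
- **Abstract, Methods**: "Primary outcome for effect size estimation is the motivational negative symptom subscale sum score of the Brief Negative Symptom Scale at" t1, corrected for baseline.
- **Primary clinical outcome**: "The primary outcome for effect size estimation is measured with the baseline-adjusted" motivation and pleasure factor of the BNSS at t1, the sum of seven items.
- **Analysis plan**, effect size: "Effect sizes between and within treatment conditions will be assessed by calculating Cohen’s" d. Neither the numerator nor the SD is stated.
- **Discussion**, use of the result: "effect sizes derived from the present study will be used for a priori sample size calculation for a subsequent fully powered RCT".

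**The concern.** A within-subject factor needs at least two levels, and this trial has two assessments in all. If t0 is reserved as the covariate, only t1 is left as outcome and time has nothing to vary over. If time keeps two levels, t0 appears on both sides of the equation. The first reading makes part of the sentence empty. The second fits a model that does not correspond to the outcome defined in the Abstract and under Primary clinical outcome, which is one post-baseline value adjusted for baseline.

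This is a conflict between stated rules, not detail left to a separate analysis plan. It matters because the effect estimate is the efficacy result that the trial is meant to pass on. The Discussion sets significance tests aside and keeps the effect size for planning the next trial. A model sentence that allows several different effect estimates, without saying which is meant, weakens that result.

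**Working it through.** **Inputs from the article.** Two assessments (t0, t1); 1:1 allocation; 15 per arm; baseline as covariate; group and time as factors. The article gives no power, alpha, SD or expected effect. Under Sample size it says: "An a priori power calculation is not appropriate for this feasibility trial as the study aim is not to test efficacy". There is therefore no planned figure to reproduce.

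**Assumed inputs, not in the article.** For the simulation: true effect −5 points, SD 7, t0–t1 correlation 0.3, 0.5 and 0.7, with 2,000 trials for each. For the sample sizes: true d of 0.3, 0.5 and 0.8, two-sided 5%, 80% power.

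**Step 1: group main effect.** Let b be the arm coefficient when the t1 score Y1 is regressed on arm and the t0 score Y0. Regressing Y0 on arm and Y0 gives an arm coefficient of exactly 0. The group main effect over both times is the arm coefficient for (Y0 + Y1)/2, so it equals (0 + b)/2 = b/2.

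**Step 2: group-by-time with baseline-by-time.** This is the arm coefficient for Y1 − Y0 adjusted for Y0: b − 0 = b, the full effect.

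**Step 3: group-by-time without baseline-by-time.** The baseline term cancels from the within-subject contrast, which leaves the raw difference in mean change. If Δ0 is the chance arm difference at t0 and β the slope of Y1 on Y0, this equals b − (1 − β)Δ0. It departs from b whenever the arms differ at baseline.

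**Step 4: simulation of Steps 1 and 2.** Mean estimates, assumed truth −5:

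| Correlation | t1 ANCOVA | Group main effect | Group-by-time with baseline-by-time |
|---|---|---|---|
| 0.3 | −4.91 | −2.46 | −4.91 |
| 0.5 | −5.03 | −2.51 | −5.03 |
| 0.7 | −5.01 | −2.51 | −5.01 |

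The ratio of main effect to t1 ANCOVA was 0.500 in every simulated trial, to rounding error.

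**Step 5: long-format models on three single simulated trials.**

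| Trial | t1 ANCOVA | Group main effect (group + time + baseline) | Group-by-time without baseline-by-time | Group-by-time with baseline-by-time |
|---|---|---|---|---|
| 1 | −10.22 | −5.11 | −9.30 | −10.22 |
| 2 | −4.47 | −2.23 | −3.93 | −4.47 |
| 3 | −3.49 | −1.75 | −5.71 | −3.49 |

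**Step 6: test and Cohen's d.** The residual of (Y0 + Y1)/2 given arm and Y0 is half the residual of Y1. Estimate and standard error therefore halve together, and the t statistic is identical. The effect on d depends on the SD chosen. At correlation 0.5, in absolute value:

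- divided by the pooled raw t0 SD: 0.74 from the t1 ANCOVA, 0.37 from the group main effect;
- divided by the model residual SD: 0.85 from both.

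**Step 7: consequence if a halved d is carried forward.** Per arm, n = 2(1.960 + 0.842)²/d² ≈ 15.70/d², rounded up.

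| True d (assumed) | n per arm at d | n per arm at d/2 |
|---|---|---|
| 0.3 | 175 | 698 |
| 0.5 | 63 | 252 |
| 0.8 | 25 | 99 |

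Halving d multiplies n by 1/(½)² = 4, apart from rounding.

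**The case against.** A reader might infer that the plan simply yields half the treatment effect. The article does not support that. It never names the group main effect as the effect estimate. A design with a between-subject group factor and a within-subject time factor is usually read through the interaction, which can return the full difference. The outcome definitions also point to the t1 ANCOVA, which returns it too. In addition, the sentence on Cohen's d is not tied to any model term. A d computed from the descriptive means and SDs that are also planned would not be affected, and nor is a d over the residual SD. These points stand, and they make the halving conditional.

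A reader might also take the fourfold sample size as the expected outcome. It requires four things together: t0 kept as an outcome, the group main effect read as the effect, division by a raw SD, and that d used without further scrutiny. The true values of d are assumptions.

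It can also be said that little depends on the model. The p-value does not change, significance tests are not to be interpreted, and the feasibility and acceptability measures do not use it. At 15 per arm, the 95% CI for a d of 0.5 runs from roughly −0.2 to 1.2, so the estimate is imprecise whatever the model. This is true, but it limits the harm and does not remove it. The article discards the tests and keeps the estimate, and wide sampling error is no reason to leave the target of estimation undefined.

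**Conclusion.** The point holds as a contradiction within the article. The Analysis plan combines a baseline covariate with a within-subject time factor, which two assessments cannot support, and the result does not match the primary outcome as defined in two other places.

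The algebra is exact and needs no assumption: the group main effect is b/2, group-by-time with baseline-by-time is b, and group-by-time without it is the raw difference in change scores. The article does not say which one is the effect estimate.

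The damage to Cohen's d and to a later sample size is conditional. If the group main effect is divided by a raw SD, d is halved and the later trial is about four times too large, as tabulated for the three assumed values of d. Under the other readings d is not halved, although the raw change-score version still differs from the baseline-adjusted difference when the arms are unequal at t0. The significance test of the group effect is the same as in the t1 ANCOVA.

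**What to change.** Remove the clause that makes time a within-subject factor and state instead: ANCOVA with the BNSS motivation-and-pleasure sum score at t1 as dependent variable, arm as factor and the t0 score as covariate; the adjusted mean difference with 95% CI is the effect estimate.

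Derive the between-group d from that difference and name the SD. The pooled t0 SD is one option; if it is used, note that the BNSS entry threshold under Eligibility criteria may restrict it and so enlarge d.

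Use the same form for secondary outcomes that have one value per time point. The EMA goal-pursuit data, collected twice daily for a week, must first be aggregated or modelled as repeated measures.

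A repeated-measures model without the baseline covariate, with group-by-time named as the effect, would also be coherent. It estimates the difference in change, however, so the outcome definition would have to be altered to match.

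The cost is one or two sentences, with no new data and no burden on participants. Trial status reports 22 of the planned 30 participants included, so when the article was written the correction could still be made before analysis.

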#### Recruitment, randomization, and blinding

Participants are recruited from outpatient settings in Hamburg (i.e., clinical psychologists and psychiatrists in private practice, social services), psychiatric clinics, and local self-help groups. Participants are either referred to the study by practitioners or via self-referral.

Enrolled and potentially eligible participants are invited for a study information meeting with a trial therapist. The participant will receive a copy of the participant information sheet which provides detailed information about the aims of the study and trial procedures. Participants are given the opportunity to ask questions. Following the information meeting, participants have sufficient time (24 h to 1 week) to consider their participation. After providing informed consent, participants meet with a trial rater who assesses eligibility and completes the baseline assessment with eligible participants. Clinical interviews are conducted by trial raters (psychologists in clinical training with at least master’s degree). All raters have already undergone training in basic therapeutic skills, such as assessment and building rapport. All raters receive a 4-h rater training by the trial manager on all of the observer-rated measures used in this trial. Allocation to either treatment- or wait-list control group is conducted (1:1) using permuted blocks of 4, 6, and 10 to reduce predictability of the sequence. The randomization schedule is generated and preserved by an assistant of the work group who is not otherwise involved in trial procedures. The trial manager is informed about the participant’s group allocation and notifies the participant and the responsible trial therapist.

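### Covariates enter the ANCOVA from an open list, by baseline significance test or by correlation with the outcome, under an analyst who knows allocation: avoidable instability and discretion in the adjusted estimate

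*Protocol article*

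**What the plan says.** The protocol article, section Analysis plan, first sets between-arm tests at baseline: "characteristics at baseline will be compared using Pearson chi-square tests for the categorical variables", with a t-test or Mann–Whitney test for quantitative variables. It then describes the clinical analysis: "Confirmatory analysis will be conducted for primary and secondary outcomes based on the ITT population", by an ANCOVA adjusted for baseline values. Covariates are added to that model by a rule with two routes: "Any variables that show significant group differences at baseline or are found to correlate with the primary outcome". The candidates are illustrated, not listed: "e.g., age, gender, diagnosis, medication doses, duration of illness, symptom severity, etc.) will be entered as covariates". No significance level, no correlation threshold and no maximum number of covariates is given.

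The section Data collection, management, and confidentiality says that "quantitative and qualitative data analyses are carried out by the trial manager and quality checked by the principal investigator". The section Recruitment, randomization, and blinding says that "The trial manager is informed about the participant’s group allocation and notifies the participant and the responsible trial therapist". The blinding described there concerns the secondary raters of the video recordings.

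The target is 30 participants, 15 per arm (Sample size). The effect on the primary outcome is meant to inform the sample size of a later full trial (abstract, Sample size and Discussion).

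**The concern.** Neither route identifies a variable worth adjusting for on grounds known in advance.

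- **Baseline significance.** Under 1:1 randomisation any significant baseline difference is chance by construction. The test says nothing about whether the variable predicts outcome, and prognosis is what makes adjustment useful.
- **Correlation with the primary outcome.** This can be applied only once outcomes are seen, so the model is chosen with the data it is meant to analyse.

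Because the list is open, someone must decide which variables to screen and where to stop. That person is the trial manager, who knows allocation. At stake is the adjusted ANCOVA estimate: two analysts could both follow the rule on the same data and report different effects.

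**Working it through.** The plan gives no figure on this point to reproduce. The check asks how often the rule changes the model, and by how much.

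**Inputs from the article:** 15 per arm; six named example covariates.

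**Assumptions:** two-sided 0.05 for both screens; independent candidates; k = 6 (the named examples) or k = 10 (for the open list); t0–t1 correlation 0.6, with 0.5 in a second set of runs. Effects are in SD units of the outcome.

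**1. What triggers entry.** The critical t on 28 df is 2.048.
- Baseline difference: 2.048 × √(2/15) = 0.75 SD.
- Correlation: 2.048 / √(28 + 2.048²) = 0.36.

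**2. Chance of at least one entry when all candidates are noise.**
- Baseline tests only, 1 − 0.95^k: 26% for k = 6, 40% for k = 10.
- Both routes, 1 − 0.95^(2k): 1 − 0.95^12 = 46% for k = 6; 1 − 0.95^20 = 64% for k = 10.

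**3. Price of one non-prognostic covariate that only just passes the baseline test.** It shares 2.048² / (2.048² + 28) = 0.13 of its variance with arm, so the standard error rises by a factor 1/√(1 − 0.13) = 1.07.

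**4. Simulation: baseline-only ANCOVA against ANCOVA plus every variable the rule admits** (t0–t1 correlation 0.6).

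| Candidates | Any enters | SD of estimate, fixed → rule | Median shift when any enters |
|---|---|---|---|
| 6, all noise | 46% | 0.297 → 0.306 (+3%) | about 0.08 |
| 10, all noise | 64% | 0.291 → 0.309 (+6%) | about 0.09 |
| 6, three prognostic (coefficient 0.3) | about 84% | 0.293 → 0.261 (−11%) | about 0.12 |

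In the noise settings the 90th percentile of the shift, when any covariate enters, is about 0.23 to 0.24 SD. In the third row, with a true effect of 0.4, the mean estimate falls from 0.396 to 0.375. The entry rate in that row was about the same with t0–t1 correlation 0.5.

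The fixed-model SD agrees with theory: √(2/15 × (1 − 0.6²)) = 0.29.

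**5. Type I error.** Applied mechanically, the rule rejects a true null in 4.4% to 5.6% of simulated trials, which is near nominal.

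**6. Discretion.** In the runs with correlation 0.5 and 6 or 12 candidates, the analyst was allowed to choose where the open list ends. Under the null, taking the smallest p-value raised rejection to between 0.06 and 0.09. Taking the most favourable estimate moved its mean by 0.03 to 0.10 SD towards treatment. This is an upper illustration of the latitude, and not a prediction of conduct.

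**The case against.** **Adjustment can help.** The named examples, such as symptom severity and duration of illness, are plausibly prognostic. The third row of the table shows that the rule can then reduce the SD of the estimate. This stands: a general claim that the rule costs precision would be wrong. The gain comes from the prognostic variables, though, and naming them in advance would keep it without the selection step.

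**The shift is small beside sampling error.** This also stands. A reader might infer that a shift of 0.08 SD around d = 0.4 would swing the next trial from about 100 per arm to about 70 or 155 (80% power, two-sided 0.05). The arithmetic is right but it overstates the rule's role: sampling error of 0.30 SD alone spans d = 0.10 to 0.70, or roughly 1,570 to 33 per arm, and a fixed model does not remove that. The documents also do not say that Cohen's d is taken from the covariate-extended model. If it comes from raw means or from the baseline-only model, the planning consequence disappears.

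**Significance tests are disclaimed.** The Discussion says that they will not be interpreted and that 30 participants are too few for reliable efficacy analysis. That limits the weight of the point, but the effect estimate is retained, and the estimate is what the rule disturbs.

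**Details may sit in the full protocol or an analysis plan.** A closed list, a cap or analyst blinding could be there, and their absence from an article is not the point. The selection rule is stated in the article, and it is the rule that is unsound. A reader might also infer that covariates chosen for the primary outcome are forced on every secondary outcome. That rests only on adjacent sentences and is not stated.

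**The principal investigator checks the analyses.** This is so, but the check is not described as blinded, and a check of execution does not constrain which variables are screened.

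**Conclusion.** The point holds as avoidable instability and analyst discretion in the adjusted ANCOVA estimate. With noise-only candidates the rule changes the model in about half to two thirds of trials, moves the estimate by a median of 0.08 to 0.09 SD when it does, and adds about 3% to 6% to its SD. With prognostic candidates it can reduce the SD (about 0.29 to 0.26), while pulling the mean estimate slightly towards zero.

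It is not a finding of inflated type I error under mechanical use, nor of precision lost in every case, nor of a demonstrated error in the next trial's sample size. The figures rest on assumed 5% thresholds, assumed candidate numbers and assumed correlations, and are illustrative. The change is worth making because it is cheap and the rule has no advantage that a prespecified model lacks.

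**What to change.** - Make the primary model arm plus the t0 value of the same outcome.
- Delete both data-driven entry rules. Describe baseline by arm, without significance tests as a selection step.
- Allow at most one sensitivity model with one or two baseline prognostic variables, named and logged as a protocol modification before any t1 outcome data are analysed. The Trial status section reports 22 participants already included, so this is not prespecification before randomisation, but it still precedes the outcome analysis.
- State that Cohen's d comes from the fixed model.
- Lock the analysis script before outcome analysis. The remedy should rest on the fixed model and the locked script, because coded arm labels would hardly blind a trial manager who "notifies the participant and the responsible trial therapist".

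The cost is wording only, with no new data, patients or procedures. The downside is no freedom to add covariates later, and possibly some lost precision if a strong prognostic variable stays out of the primary model.

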**Discussion:**

The feasibility and acceptability data will be used to improve trial procedures and the “Goals in Focus” intervention where necessary. The treatment effect on the primary outcome will provide the basis for the sample size calculation for a fully powered RCT.

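### Cohen's d, the effect size the plan names, is biased away from zero by about 3% on average at 15 per arm; Hedges' g with its confidence interval is the better figure to hand on

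*Protocol article*

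**What the plan says.** The Analysis plan section of the protocol article names the effect measure: "Effect sizes between and within treatment conditions will be assessed by calculating" Cohen's d. It does not say which standard deviation is the divisor. It neither mentions a small-sample correction nor excludes one.

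Under Sample size, "the target for this feasibility study was set at" 30, with 15 in each group and 1:1 allocation. No power, significance level or assumed effect is given. The section explains: "An a priori power calculation is not appropriate for this feasibility trial as the study aim is not to test efficacy".

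The effect size nevertheless has a stated use. The Discussion paragraph of the abstract says: "The treatment effect on the primary outcome will provide the basis for the sample size calculation for a fully powered RCT". The main Discussion repeats that "effect sizes derived from the present study will be used for a priori sample size calculation for a subsequent fully powered RCT". It also concedes that "the sample of 30 participants is not sufficient for a reliable efficacy analysis" and that "the wait-list comparator may artificially inflate estimates of the intervention effect". It does not mention the small-sample bias of d.

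**The concern.** A sample standard deviation in the denominator makes Cohen's d biased away from zero when few participants contribute to it. The size of this bias is known exactly under normal data, and Hedges' g removes it. A reader who applies the Analysis plan literally computes the uncorrected value.

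The bias matters here, if only a little, because the article says that significance tests from this trial cannot be interpreted and that the effect size goes forward to plan the next trial. Required sample size varies as one over the square of the effect, so a proportional error in d is roughly doubled in n. When the true effect favours the intervention, the bias also acts in the same direction as the wait-list inflation that the Discussion acknowledges.

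**Working it through.** The article gives no power-based figure to reproduce, because 30 was set from recommendations and comparable trials. The check is therefore of the bias itself.

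**Inputs from the article**
- Cohen's d as estimator (Analysis plan).
- 15 per arm (Sample size).
- 1:1 allocation (Recruitment, randomization, and blinding).

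**Assumptions, not in the article**
- Normal outcomes with equal variances.
- For illustration: true effect 0.5, two-sided 5% level, 80% power.

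**Step 1: correction factor.** With m degrees of freedom in the standardiser, the expected value of d is the true effect divided by J(m), where J(m) = Γ(m/2) / [√(m/2) · Γ((m−1)/2)]. The familiar approximation is 1 − 3/(4m−1).

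| Standardiser | m | J(m) | Approximation | Average excess, 1/J − 1 |
|---|---|---|---|---|
| Pooled SD, 15 + 15 | 28 | 0.9729 | 0.9730 | 2.8% |
| ANCOVA residual SD, one covariate | 27 | 0.9719 | 0.9720 | 2.9% |
| Pooled SD, 22 contributing (illustration) | 20 | 0.9619 | 0.9620 | 4.0% |
| Single-arm SD, 15 | 14 | 0.9453 | 0.9455 | 5.8% |

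The percentage thus depends on a choice that the Analysis plan does not state. A within-arm effect divided by the pooled two-arm SD has 28 degrees of freedom and a bias of 2.8%, not 5.8%.

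**Step 2: bias against sampling error.** At a true effect of 0.5 and 15 per arm, the expected d is 0.5/0.9729 = 0.514, a bias of 0.014. In 400,000 simulated trials:
- The mean of d was 0.514 and its SD 0.386, with a 95% range of −0.22 to 1.30.
- The bias is 0.014/0.386, about 0.035 of one SD.
- Uncorrected d exceeded 0.5 in 50.5% of trials, and g did so in 49.0%.
- At a true effect of zero the mean of d was zero to three decimals.

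**Step 3: gain from the correction.** The mean squared error of d is 0.386² + 0.014² ≈ 0.149. Since g = 0.9729 · d is unbiased, its mean squared error is (0.9729 × 0.386)² ≈ 0.141. That is about 5% lower.

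**Step 4: effect on the later trial's size.** J(28)² = 0.9466, so a trial sized from the expected d is 1 − 0.9466 = 5.3% smaller than one sized from the true effect. Equivalently, 1/0.9466 − 1 = 5.6% more participants would be needed. By noncentral t this is 61 against 64 per arm at a true effect of 0.5, and 61 per arm gives 78.2% power.

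That result applies only if the pilot returns exactly its expected d. At the median pilot result d is about 0.505 and g about 0.491. These give 63 and 67 per arm, against the 64 that the true effect needs.

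**The case against.** The strongest objection is that the article only names Cohen's d. The exact formula, the standardiser and any correction are details that a condensed article may leave to the full protocol or statistical analysis plan, and neither is shown. Some authors also use d loosely for the corrected value. It is therefore not established that an uncorrected d will be computed. What remains is that the article does name an estimator, and as ordinarily defined that estimator is the biased one. Naming g instead is a definite improvement.

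The second objection is materiality. It stands almost in full. A bias of 0.014 beside a sampling SD of about 0.39 will not decide anything, and the Discussion already admits the larger problems of a small sample and a wait-list comparator.

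A reader might infer two stronger statements, and neither is supported:
- **That every reported effect size will be overstated.** The bias is a property of the average. At a true effect of 0.5 nearly half of uncorrected estimates fall below the truth, and at zero effect there is no bias.
- **That the later trial will be about 5% too small.** This holds only when sizing from the expected d. At the median result, uncorrected d gives 63 per arm, closer to the required 64 than the 67 from g. Because n varies as one over the square of the effect, an unbiased effect estimate does not give an unbiased n.

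Nor is it safe to say that drop-out always increases the bias. If d is scaled by the baseline SD, participants lost later still contribute to the standardiser.

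**Conclusion.** The point holds as a small refinement. At 15 per arm, Cohen's d is biased away from zero on average by about 2.8% between arms, and by about 5.8% within an arm if a single-arm SD is the divisor. These figures rest on normal data, equal variances and full retention. The exact percentage moves with the standardiser, which the Analysis plan leaves open.

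The bias is absent at a true effect of zero and is far smaller than sampling error. No claim about an undersized later trial follows from it. The reasons to act are that g is unbiased, has about 5% lower mean squared error at a true effect of 0.5, and is practically free. The correction does not make a point estimate from 30 participants a sound basis for sizing a trial, so the interval must go forward with it.

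**What to change.** In the Analysis plan:
- State the standardiser for the between-arm and the within-arm effects.
- Replace Cohen's d by Hedges' g, that is, d multiplied by the exact gamma-function factor J(m) for that standardiser's degrees of freedom.
- Report g with its confidence interval, and state that the interval, not the point estimate alone, goes into the later sample size calculation.

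If g is already intended, naming it is enough. The cost is one line of code and one or two sentences of text. The downside is that reported effects become slightly smaller: by 2.7% between arms (1 − 0.9729), and by 5.5% within an arm with a single-arm SD (1 − 0.9453).
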